#### Inclusion and exclusion criteria

2.1.1.

Participants will be recruited from the International Medical Center and from the Departments of Emergency Medicine and of Anesthesiology at West China Hospital of Sichuan University. Four cohorts of 40 individuals each will be recruited: heatstroke patients, sepsis patients, patients undergoing CPB, and healthy controls. The inclusion and exclusion criteria for each cohort are shown in Table 1. Participant recruitment and data collection will begin on January 1, 2023 and will continue until October 31, 2023.

**Table 1 tab1:** Inclusion and exclusion criteria for subject enrollment.

Subjects	Inclusion criteria	Exclusion criteria
Heatstroke patients	(1) Age ≥ 18 years	(1) Pregnant women.
	(2) History of exposure to extreme environmental heat or vigorous muscle exertion	
	(3) Core body temperature > 40°C or symptoms of central nervous system (CNS) dysfunction, such as coma, delirium, or convulsions	(2) Comorbid with immune system disease within the 6 months prior to admission, including but not limited to acquired immune deficiency syndrome (AIDS), multiple myeloma, rheumatoid arthritis, systemic lupus erythematosus, multiple sclerosis, myasthenia gravis, scleroderma, Crohn’s disease, and ulcerative colitis.
	(4) Written informed consent to participate	
Sepsis patients	(1) Age ≥ 18 years	(3) Comorbid with malignant tumor and hematological diseases.
	(2) Suspected or known infection	
	(3) Sequential organ failure assessment (SOFA) score ≥ 2	
	(4) Written informed consent to participate	(4) History of organ or bone marrow transplantation.
Patients undergoing CPB	(1) Age ≥ 18 years	
	(2) Valve replacement or coronary artery bypass under cardiopulmonary bypass	
	(3) Written informed consent to participate	
Healthy controls	(1) Age ≥ 18 years	(5) History of immunosuppressive therapy, including glucocorticoids, soluble microbial products (SMSs), polyclonal and monoclonal antibodies, antimetabolite and alkylating agents, or radiotherapy within the 6 months prior to admission.
	(2) Body mass index 18–24 kg/m^2^	
	(3) Health examination within the previous 6 months indicated no abnormality	
	(4) Written informed consent to participate	

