#### Participant matching

2.1.2.

Heatstroke patients will be matched 1:1 with sepsis patients, CPB patients and healthy controls using propensity score analysis based on nearest-neighbor matching and a caliper width of 0.2 of the standard deviation of the logit of the propensity score (20). Covariates during matching of heatstroke and sepsis patients will be sex, age, body weight, Sequential Organ Failure Assessment (SOFA) score (21), comorbidities, and treatment history. Covariates during matching of heatstroke and CPB patients will be sex, age, body weight, comorbidities, and treatment history. Covariates during matching of heatstroke patients and healthy controls will be sex, age, and body weight.

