Additional information will be recorded onto case report forms for the three patient cohorts. In the case of heatstroke and sepsis patients, the location of onset, symptoms, and vital signs on admission will be collected. In the case of CPB patients, preoperative data will be recorded on surgical diagnosis, New York Heart Association cardiac function classification, and EuroSCORE II, as will intraoperative data about surgical procedure, surgery time, anesthesia time, amount of blood transfusion, urine output, and medicines used during surgery. We will record mechanical ventilation, renal replacement therapy, and transfusion, as well as use of vasoactive agents, glucocorticoids, and antibiotics during hospitalization for the three patient cohorts. These groups will be followed up at 30 days after admission, either in person if the individual remains in hospital or by telephone or WeChat if the individual has been discharged. During follow-up, data will be collected on death, infection, and complications affecting cardiovascular, respiratory, nervous, digestive, or urinary systems.

These data will be entered onto case report forms. To protect confidentiality, the files will be stored in a secure and locked place and manner, and the subject identification and private information will be deleted from all study documents. To control the quality of data, supervising investigators will be required to ensure the accuracy and completeness of the data. Then the data will be doubly entered into the EpiData 3.10 database system by two investigators. After finishing the data entry and dealing with the query, the database will be locked under the orders of the principal investigator. No one is allowed to view the database without authorization; otherwise, they should notify the principal investigator.

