#### Blood collection

2.4.1.

Venous blood (10 mL) will be collected into tubes coated with ethylenediamine tetraacetic acid within 24 h after admission in the case of heatstroke and sepsis patients, at the end of CPB in the case of CPB patients, and during outpatient visits at the International Medical Center in the case of healthy controls.

Within 4 h after collection, 8 mL of the blood samples will be processed to isolate peripheral blood mononuclear cells (PBMCs; see section 2.4.2), while the remaining 2 mL of blood will be centrifuged at 100 *g* at 4°C for 5 min, and then 500 μL of plasma will be stored at −80°C for cytokine assays (see section 2.4.5).

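### The immunosuppression exclusion looks back from admission, not from the blood draw, so glucocorticoids given in between are neither excluded, matched nor adjusted for and could pass as disease or prognostic signals

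*Protocol article*

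**What the plan says.** Table 1 (section 2.1.1), exclusion criterion (5), opens with "History of immunosuppressive therapy, including glucocorticoids, soluble microbial products (SMSs), polyclonal and monoclonal antibodies" and ends with "antimetabolite and alkylating agents, or radiotherapy within the 6 months prior to admission".

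Section 2.4.1 sets one sampling time per cohort: "within 24 h after admission in the case of heatstroke and sepsis patients", then "at the end of CPB in the case of CPB patients, and during outpatient visits at the International Medical Center" for healthy controls.

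Section 2.4 says that mechanical ventilation, renal replacement therapy and transfusion will be recorded, "as well as use of vasoactive agents, glucocorticoids, and antibiotics during hospitalization for the three patient cohorts". For CPB patients it also records "amount of blood transfusion, urine output, and medicines used during surgery". Table 2 places transfusion and medication use at Visit 2, during hospitalization, with no reference to the blood draw.

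On matching, section 2.1.2 states: "Covariates during matching of heatstroke and CPB patients will be sex, age, body weight, comorbidities, and treatment history". Heatstroke against sepsis adds the SOFA score, and healthy controls are matched on sex, age and body weight only. The treatments listed in section 2.4 are antihypertensives, aspirin, statins, anticoagulants, oral antidiabetics, insulin and levothyroxine.

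Section 2.5 compares cohorts by t-test, ANOVA or rank tests, compares immune subsets by heatstroke prognosis with a t-test or Mann–Whitney test, and assesses diagnostic and prognostic ability by ROC curves. It names no adjustment for drugs given before sampling.

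**The concern.** By naming glucocorticoids in criterion (5), the protocol treats recent use as incompatible with a usable immune profile. The criterion does not reach the exposure closest to the measurement. Read literally, a short steroid course five months before admission disqualifies a patient, while a dose given an hour before the tube is filled does not.

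The three sampling settings (emergency admission, end of cardiac surgery, outpatient visit) make unequal exposure plausible. Within heatstroke, treatment may follow severity. If so, a drug-induced shift in a lymphocyte, monocyte or granulocyte subset could be read as a signature separating heatstroke from sepsis, CPB or health, or as a marker of 30-day death. Those two readings are the aims of the study (section 2.2).

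**Working it through.** **1. The gap, cohort by cohort**

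| Cohort | Window in criterion (5) closes | Blood drawn | Interval not covered |
|---|---|---|---|
| Heatstroke | Admission | 0 to 24 h after admission | Up to 24 h |
| Sepsis | Admission | 0 to 24 h after admission | Up to 24 h |
| CPB | Admission | End of bypass | Any preoperative stay, plus the operation up to the end of bypass |
| Healthy | No admission | Outpatient visit | Window has no anchor |

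**2. Does anything else stated close it?**

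- Eligibility: no other criterion in Table 1 refers to treatment after admission.
- Matching: treatment history is a covariate for sepsis and CPB, but the listed treatments are long-term medication recorded at baseline, with no glucocorticoid or other immunosuppressant among them.
- Analysis: the named tests and ROC curves are unadjusted.
- Data: in-hospital glucocorticoids are recorded. Nothing says whether the record will show if a dose came before or after the draw, and an adjustment would need that.

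**3. Scale, under assumed inputs**

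The protocol gives no power, SD or effect size, so it has no figure of its own to reproduce. From the document: n = 40 per cohort, two-sided alpha 0.05. Assumed: no true disease difference, within-cohort SD of 1, drug effect d (in SD) on a cell subset, a share p exposed before the draw in one cohort and none in the other.

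- Spurious mean difference: p × d.
- Variance in the partly exposed cohort: 1 + p(1 − p)d², because it mixes exposed and unexposed patients.
- Standard error: √{[1 + p(1 − p)d²]/40 + 1/40}.
- Rejection rate (normal approximation): Φ(p·d/SE − 1.96) + Φ(−p·d/SE − 1.96).
- Apparent AUC: (1 − p) × 0.5 + p × Φ(d/√2).

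For p = 0.5 and d = 1: shift 0.50; SE = √(1.25/40 + 1/40) = 0.237; ratio 2.11; rejection rate 56%. Direct simulation of the t-test (200,000 data sets) gives 55%. AUC = 0.25 + 0.5 × 0.760 = 0.63.

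For p = 0.1 and d = 1: shift 0.10; SE = √(1.09/40 + 1/40) = 0.229; ratio 0.44; rejection rate 7%.

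Simulated rejection rates and apparent AUC:

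| Difference in exposed share | d = 0.5 SD: rejection, AUC | d = 1.0 SD: rejection, AUC |
|---|---|---|
| 10 points | 5%, 0.51 | 7%, 0.53 |
| 30 points | 10%, 0.54 | 24%, 0.58 |
| 50 points | 19%, 0.57 | 55%, 0.63 |
| 100 points | 60%, 0.64 | 99%, 0.76 |

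Ignoring the mixture variance and treating exposure as a uniform shift gives 26% and 60% for the 30- and 50-point cells at d = 1, which slightly overstates them. The nominal rate is 5%.

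**The case against.** Several points on the other side have force.

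- **Exposure before the draw is possible, not shown.** A reader might infer from the recording of in-hospital glucocorticoids that the protocol expects them before sampling. It records them over the whole hospital stay, and 24 h is an upper limit on the draw. Only for CPB must sampling follow intraoperative medicines, and the protocol does not say which. This stands: drug effects could enter the contrasts, but the document does not show that they will.
- **Criterion (5) may be meant to screen pre-existing immune status.** It speaks of history and shares its 6-month window with the immune-disease criterion. That reading is fair. It leaves treatment after admission without any stated rule, so the gap remains.
- **Transfusion is a separate matter.** A reader might infer that criterion (5) was meant to deal with it too. The criterion does not mention transfusion, so it belongs here only as another recorded exposure whose timing matters.
- **Excluding every exposed patient has its own cost.** If treatment follows severity, exclusion selects milder heatstroke, which matters for the 30-day mortality analysis and for recruiting 40 per cohort in ten months. This stands, and it argues against making restriction to unexposed patients the primary analysis.
- **An unseen analysis plan or case report form could deal with it.** It could add an adjustment or a time field. It would not remove the mismatch between an eligibility window and a sampling time that are both fixed in this article.

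**Conclusion.** The mismatch is on the face of the protocol: the exclusion stops at admission, the sample comes later, and nothing stated bridges the interval. For healthy controls the anchor is undefined, though this is a matter of wording, since enrolment is the obvious reading.

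The consequence is conditional. It needs exposure before the draw to differ between cohorts, or by severity within heatstroke, and the document gives neither exposure rates nor drug effects. Across the assumed range, the false-positive rate runs from about the nominal 5% to 7% (10-point difference) to about 55% (50 points, 1 SD effect). The 99% figure needs all of one cohort and none of the other to be exposed. A reader might conclude that the planned contrasts are already confounded, but the documents support only that such confounding could enter unchecked and, without timing data, might not be separable afterwards. For an exploratory study this is an inexpensive improvement, not a fatal flaw.

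**What to change.** Reconcile criterion (5) with section 2.4.1 in one of two ways:

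1. Anchor the 6-month look-back to study blood collection for the patient cohorts and to enrolment for healthy controls; or
2. Keep the admission anchor for patients, anchor healthy controls to enrolment, and state that in-hospital exposure before the draw is allowed.

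These are alternatives: under the first, no glucocorticoid-exposed patients remain to analyse. Under the second, record whether each dose of a glucocorticoid or other immunosuppressant came before or after the draw and, for CPB, do the same for each intraoperative medicine and transfusion. Then repeat the cohort comparisons and the heatstroke prognostic comparisons excluding, or adjusting for, patients exposed before the draw. Where exposure nearly coincides with cohort membership, as it might for CPB, no adjustment can separate the two, and that contrast should be reported as confounded.

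The second route costs one time field on items already collected and a sensitivity analysis in a smaller, possibly less severe subset. The first costs some recruitment and may select milder cases. Neither changes clinical care.

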#### Participant matching

2.1.2.

Heatstroke patients will be matched 1:1 with sepsis patients, CPB patients and healthy controls using propensity score analysis based on nearest-neighbor matching and a caliper width of 0.2 of the standard deviation of the logit of the propensity score (20). Covariates during matching of heatstroke and sepsis patients will be sex, age, body weight, Sequential Organ Failure Assessment (SOFA) score (21), comorbidities, and treatment history. Covariates during matching of heatstroke and CPB patients will be sex, age, body weight, comorbidities, and treatment history. Covariates during matching of heatstroke patients and healthy controls will be sex, age, and body weight.

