Therefore, the aims of this case–control study are to identify the specific immune cells biomarker(s) to diagnose heatstroke and predict prognosis by exploring the immune profile of heatstroke as it differs from profiles in aseptic inflammation and sepsis. The results will help us more comprehensively understand the immune system characteristics of heatstroke, improve its diagnosis, and provide a basis for the development of immunotherapy. In the trial, patients with heatstroke, patients with sepsis, patients undergoing cardiopulmonary bypass [CPB, representative of aseptic inflammation (19)], and healthy controls will be compared in terms of their profiles of lymphocytes, monocytes, natural killer cells, and granulocytes in circulation, based on flow cytometry; in terms of gene expression in different immune cell populations, based on single-cell RNA sequencing; and in terms of cytokine levels in plasma, based on enzyme-linked immunosorbent assay (ELISA). The three cohorts of patients will be matched according to age, sex, weight, and comorbidities. Healthy controls will be matched to heatstroke patients based on age, sex and weight.

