### Study protocol

2.4.

Specially trained investigators will screen individuals for potential inclusion based on the inclusion and exclusion criteria, and they will obtain written informed consent from the individuals or their legal representatives. The items to be measured are listed in Table 2. The following baseline data will be recorded from all participants on case report forms: age, sex, ethnicity, profession, education level, body mass index, history of smoking and drinking, family medical history, laboratory results, comorbidities, and treatments. Comorbidities include cardiovascular disease, hypertension, asthma, chronic obstructive pulmonary disease, epilepsy, stroke, diabetes, hyperthyroidism, hypothyroidism, chronic liver disease, virus infection, and neurological disease. Treatments include antihypertensive agents, aspirin, statins, anticoagulant drug, oral antidiabetic agents, insulin, and levothyroxine.

**Table 2 tab2:** Schedule of enrollment, intervention, and assessment.

Items	Screening	Post-allocation	1 month after trial
	Visit1 (Within 24 h of admission)	Visit2 (During hospitalization)	Visit3
Informed consent	**×**		
Inclusion/exclusion criteria	**×**		
Basic information^a^	**×**		
Smoking and drinking history	**×**		
Family medical history	**×**		
Comorbidities and treatments^b^	**×**		
The location of onset, symptoms and vital signs on admission (for heatstroke patients and sepsis patients)	**×**		
Preoperative data (for CPB patients)		**×**	
Intraoperative data (for CPB patients)		**×**	
Mechanical ventilation		**×**	
Renal replacement therapy		**×**	
Transfusion		**×**	
Usage of medication^c^		**×**	
Death			**×**
Infection			**×**
Complications^d^			**×**

a Age, gender, job, height, and weight, etc.

b Comorbidities include cardiovascular disease, hypertension, asthma, chronic obstructive pulmonary disease, epilepsy, stroke, diabetes, hyperthyroidism, hypothyroidism, chronic liver disease, virus infection, and neurological disease. Treatments include antihypertensive agents, aspirin, statins, anticoagulant drug, oral antidiabetic agents, insulin, and euthyrox.

c Including vasoactive agents, glucocorticoids, and antibiotics.

d Including cardiovascular, respiratory, nervous, digestive or urinary systems complications.

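### In the heatstroke-versus-healthy contrast only, chronic disease and long-term treatment are confounded with case status, and no stated analysis separates them

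*Protocol article*

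**What the plan says.** **Controls.** Table 1 (section 2.1.1) admits a healthy control only if the "Health examination within the previous 6 months indicated no abnormality", and also sets "Body mass index 18–24 kg/m^2".

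**Heatstroke patients.** Table 1 asks for adult age, heat exposure or exertion, hyperthermia or central nervous system signs, and consent. The exclusions are pregnancy, immune system disease (AIDS is named), malignant or haematological disease, transplantation, and recent immunosuppressive therapy. Section 2.4 then lists what is recorded at baseline: "Comorbidities include cardiovascular disease, hypertension, asthma, chronic obstructive pulmonary disease, epilepsy, stroke, diabetes, hyperthyroidism, hypothyroidism, chronic liver disease, virus infection, and neurological disease". It also records seven kinds of long-term drug, from antihypertensives to levothyroxine. None of these 12 conditions is an exclusion as such.

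**Matching (section 2.1.2).**
- Sepsis: "Covariates during matching of heatstroke and sepsis patients will be sex, age, body weight, Sequential Organ Failure Assessment (SOFA) score (21), comorbidities, and treatment history".
- CPB: "Covariates during matching of heatstroke and CPB patients will be sex, age, body weight, comorbidities, and treatment history".
- Healthy: "Covariates during matching of heatstroke patients and healthy controls will be sex, age, and body weight". The Introduction agrees: "Healthy controls will be matched to heatstroke patients based on age, sex and weight".

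**Analysis (section 2.5).** Cohorts are compared by ANOVA, t-test, Kruskal-Wallis or Mann-Whitney test, followed by ROC curves with Youden thresholds, sensitivity, specificity, predictive values and likelihood ratios. No adjustment or restriction for comorbidity is stated.

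**Use of the contrast.** Section 2.2 includes healthy individuals among the groups from which a diagnostic marker should distinguish heatstroke.

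**The concern.** By matching on comorbidities and treatment history against sepsis and CPB, the protocol treats both as confounders. In the healthy contrast they are not matched, and there the imbalance is greatest by design: some share of heatstroke patients against essentially none of the controls. The Discussion says that matching is meant to reduce bias from clinicodemographic differences among all four cohorts. For this confounder, matching on sex, age and weight does not do that.

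At stake is how the immune profile of heatstroke relative to health is read. A subset shifted by diabetes, liver disease or a long-term drug would show a difference from controls, and some apparent ROC accuracy, with no contribution from heatstroke. Where heatstroke does change the subset, the estimate would be shifted by the comorbidity effect and so be exaggerated or partly masked. The bias is systematic: recruiting more patients would not remove it.

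**Working it through.** **1. What the plan's own figures allow.** There is no power-based figure to reproduce. Section 2.3 says that no sample size was calculated, and 40 per cohort is set by precedent. The documents give neither the share of heatstroke patients with a comorbidity nor the effect of comorbidity on any subset.

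**2. The contrasts side by side.**

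| Contrast | Comorbidities matched | Treatment history matched | Comorbidity possible in comparator |
|---|---|---|---|
| Heatstroke v sepsis | yes | yes | yes |
| Heatstroke v CPB | yes | yes | yes |
| Heatstroke v healthy | no | no | essentially no |

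The last cell shows why adding comorbidities to the healthy-control propensity model would not help. With no overlap there is nothing to match or adjust on.

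**3. Size under stated assumptions.** Inputs from the documents: n = 40 per cohort (section 2.1.1), two-sided 0.05 (section 2.5). Assumed: p, the share of heatstroke patients with a comorbidity, 30–70% (0% in controls); d, its effect on a subset, 0.3–0.8 SD; no effect of heatstroke itself.

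- Shift = p × d
- Standard error = √[(2 + p(1 − p)d²)/40]
- Rejection probability = 1 − Φ(1.96 − shift/SE) + Φ(−1.96 − shift/SE)
- AUC = p × Φ(d/√2) + (1 − p) × 0.5

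Central case, p = 0.5 and d = 0.5: shift = 0.25 SD; SE = √(2.0625/40) = 0.227; ratio = 1.10; rejection = 19.6%; AUC = 0.57.

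| p | d | Shift (SD) | Rejection, simulated t-test (3,000 runs) | Rejection, formula | AUC |
|---|---|---|---|---|---|
| 0.3 | 0.3 | 0.09 | 6.1% | 6.9% | 0.53 |
| 0.3 | 0.5 | 0.15 | 10.2% | 10.2% | 0.54 |
| 0.5 | 0.5 | 0.25 | 18.9% | 19.6% | 0.57 |
| 0.7 | 0.5 | 0.35 | 35.0% | 33.9% | 0.60 |
| 0.7 | 0.8 | 0.56 | 65.8% | 67.9% | 0.65 |

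The two methods agree closely. With comorbidity balanced between the groups, the shift is 0 and rejection returns to 5%.

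**4. What a restricted analysis can show.** At p = 70% to 30%, 40 × (1 − p) leaves 12 to 28 pairs. Treating the groups as independent, the 95% half-width is t × √(2/n):
- n = 12: 2.074 × 0.408 = 0.85 SD
- n = 28: 2.005 × 0.267 = 0.54 SD

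Both exceed the central shift of 0.25 SD. Restriction removes this bias from the estimate, but the comparison with the full result cannot reliably detect a bias of that size.

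**The case against.** **The other contrasts act as a screen.** Section 2.2 looks for markers that separate heatstroke from sepsis, from aseptic inflammation and from health. A subset shifted only by chronic disease should be roughly balanced in the sepsis and CPB contrasts and would tend not to separate heatstroke from either. The Introduction and Discussion also place the clinical difficulty in telling heatstroke from those conditions, not from health. This stands, and it limits the harm. It is not complete protection, because section 2.5 states no rule that a marker must pass all three contrasts.

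**The omission is coherent.** A disease-free reference group cannot be matched on comorbidity, and sections 1 and 2.1.2 agree on the healthy-control covariates. This stands: the list is not a slip or a contradiction. The confounding follows from the design all the same.

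**A sensitivity analysis may be in documents not shown.** That is possible, so its absence from an article is not the finding. The finding rests on what the article does state: eligibility, matching covariates and unadjusted tests.

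**Strongly immune-altering conditions are already excluded.** Immune disease, malignancy, haematological disease, transplantation and recent immunosuppression are out. This stands and makes the upper end of the assumed effect range less plausible. It also means that not every condition under the 12 headings is admitted; AIDS, for example, is not.

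**The study is exploratory.** That excuses low power, but not a foreseeable systematic difference. It does argue for a modest remedy.

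**Conclusion.** The point holds for one of the three contrasts. As stated, the plan yields a heatstroke-versus-healthy comparison in which chronic disease and long-term treatment cannot be separated from heatstroke. The consequence falls mainly on descriptive statements and ROC accuracy relative to health.

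The direction of the problem follows from the design; its size cannot be found from the documents. The range of about 6–66% false positives per unaffected subset depends entirely on assumed values of p and d. It also treats 12 dissimilar conditions as one factor that moves a subset by the same amount in the same direction. It spans negligible to serious and should be read as an illustration.

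A reader might infer more than this:
- *That a subset altered by chronic disease would end up labelled a diagnostic heatstroke biomarker.* The documents do not support this, because the sepsis and CPB contrasts match on comorbidities and treatment history and would tend to screen it out.
- *That matching on more covariates would solve it.* It would not, because the controls have essentially no comorbidity.
- *That the Introduction promises balance on treatments for the patient cohorts.* It names comorbidities only; treatment history appears in section 2.1.2.

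**What to change.** In section 2.5, for the heatstroke-versus-healthy contrast:

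1. Pre-specify a sensitivity analysis restricted to heatstroke patients with none of the comorbidities or long-term treatments listed in section 2.4, with their matched controls. Report the estimate and 95% interval beside the full-cohort result.
2. Show the mix of classic and exertional heatstroke in the restricted set.
3. Do not attach a pass/fail rule. With about 12–28 pairs the intervals are too wide for one, and any threshold for agreement would be arbitrary.
4. State that the full-cohort healthy contrast is a descriptive reference. Base diagnostic biomarker claims on subsets that also separate heatstroke from the comorbidity-matched sepsis and CPB cohorts.

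**Cost.** One further analysis and two or three sentences of text. Comorbidities and treatments are already recorded for all participants, so no recruitment or assay is added. The restricted analysis will be imprecise. It may also over-represent exertional heatstroke, which section 2.5 describes as a condition of young people, so a difference between restricted and full results could reflect heatstroke type or age as well as removed confounding. Item 2 is there to make that visible.
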